#### B. Physical tests

##### Physical examination of the cervical spine

The cervical spine is examined using a manual rotation test and a pain provocation test.

The rotation test is performed for both rotations (left and right) at the C0-2 and C2-7 regions. It is scored for mobility (hyper/hypo or normal), endfeel (too hard, normal, too soft or empty) and for the onset of pain (yes/no). The test is considered positive if two out of three criteria were positive, i.e. hyper- or hypo-mobility, too hard or soft or empty endfeel, and the provocation of pain.

The pain provocation test is the adapted Spurling test (passive lateral flexion, homolateral rotation, extension and axial compression at the end). It is performed on all segments starting at C0-1 and descending till C6-7. It is scored for pain provocation and endfeel. When pain is provoked during this test, a VAS (0 mm – 100 mm) is recorded. If subjects rate their pain > 20 mm on a VAS, this test is considered positive.

These tests can discriminate between asymptomatic controls and patients with neck pain [35]. In this study we apply them to identify an underlying painful segmental dysfunction.

##### Thermal and pressure stimuli

Thermal and pressure stimuli are used to detect sensitisation. Stimuli are applied in cranial and extra-cranial regions. To screen for central sensitization, measurements were also taken on the dorsal side of the index, on the tibialis anterior (pressure) and on the thenar (temperature).

Thermal stimuli will be investigated using the TSA II Thermotest (Medoc Advanced Medical Systems Ltd. [name]). A thermode of 30 × 30 mm is attached first to the skin of the hand (palmar thenar, C6), next to the mastoid process (C2) and finally to the temple (trigeminal nerve). Starting from a baseline temperature of 32°C, the intensity of the stimulus will vary following the method of limits protocol (+/- 1°C/s). Four modalities are tested: cold and warm sensation (CS and WS) and cold and heat pain detection thresholds (CP and HP). First subjects are asked to press a button as soon a change in temperature is perceived (CS and WS, 4 stimuli). Second they have to push the button when the temperature stimulus is perceived as unpleasant/painful (CP and HP, 3 stimuli). All measurements are performed bilaterally. The average of the repetitions is used for further calculations.

The sequence of the thermal stimuli is chosen to familiarise the subjects with the test: it is reassuring to have the first set of stimuli on the hand and not on the head, which is the site of the complaints. This method has been shown to be reliable [36].

Pressure stimuli are measured using a hand held algometer (Somedic AB, Farsta, Sweden). Pain detection thresholds will be measured on the temple, the mastoid process, the dorsal side of the index and on the tibialis anterior muscle. The average of three measurements will be used for further calculations. Subjects have to report when the feeling of pressure alone changes into a feeling of pressure and pain.

Quantitative Sensory Tests are psychophysical tests. To increase the reliability and ecological validity of the tests, all measurements will be performed at the participants' home.

### Follow-up measurements

After approximately 7, 12, 26 and 52 weeks, participants will be asked to complete the Headache Inventory List and HIT-6 again. For all questionnaires a recall period of four weeks is chosen, in correspondence with the recall period of the HIT-6.

The global perceived effect (GPE) is measured using a 7 point scale, ranging from 'completely recovered' to 'worse than ever'. This way of measuring GPE has been used in similar studies in which the effect of commonly applied therapeutic approaches have been compared [37,38]. Responders (positive effect) and non-responders (no effect or worse) can be identified.

The follow-up measurements are also available online ensuring a blinded rater assessment. The questionnaires which are returned in paper version (from participants without internet connection) will be inserted in the software by an independent blinded rater.

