## Methods/design

### Study design

A randomised clinical trial with blinded assessment and unblinded treatment and with a follow-up period of 12 months was developed. The research protocol was approved by the Medical Ethics Committees of the University Hospital of the Vrije Universiteit Brussel (UZ Brussel) and of the University Hospital of Antwerp (UZA).

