#### A. Questionnaires

All questionnaires can be completed online using PHP-surveyor [29]. In case a participant does not have the opportunity to fill in the questionnaires online, a paper version including an addressed and stamped envelope is provided. The rater is blinded: the online version is completed by the participants themselves, the paper versions are inserted in the computer software by an independent, blinded rater.

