#### Primary and secondary outcome measures

Two primary outcome measures will be used in this study: GPE and the HIT-6 score.

Reduction in headache frequency, headache pain intensity, medication intake, absenteeism and looking for professional help will be used as secondary outcome measures.

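### Follow-up assessment is described as blinded, but every follow-up outcome is self-reported by patients who know their treatment arm

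*Protocol article*

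**What the plan says.** Under Study design the trial is called "A randomised clinical trial with blinded assessment and unblinded treatment". Under Follow-up measurements the assessment claim is repeated for the period after randomisation: "The follow-up measurements are also available online ensuring a blinded rater assessment". For patients without internet access, paper forms "will be inserted in the software by an independent blinded rater".

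The same section sets out what is measured at about 7, 12, 26 and 52 weeks: "participants will be asked to complete the Headache Inventory List and HIT-6 again". It adds the GPE, a seven-point scale of perceived change that is split into responders and non-responders. Under Primary and secondary outcome measures: "Two primary outcome measures will be used in this study: GPE and the HIT-6 score". The secondary outcomes are headache frequency, pain intensity, medication, absenteeism and care-seeking, which are the contents of the Headache Inventory List.

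**The concern.** For a self-completed questionnaire the assessor is the patient. After randomisation the patient in the usual care plus physiotherapy arm (UCMT) knows that physiotherapy was given, and the patient in the usual care arm (UC) knows that it was not. An assessment made by that person is not blinded, whatever the medium of the form.

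What is at stake is the credit given to the UCMT–UC comparison. Someone who rates the trial on the stated design would record blinded outcome assessment for both primary outcomes, GPE and HIT-6, and would discount expectation and reporting bias accordingly. GPE asks directly how much the patient feels helped. It is also the outcome on which the sample size rests and the one that defines the responder status in the prognostic model.

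**Working it through.** **Step 1. Who rates what, and when.**

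| Measurement | Timing | Who supplies the rating | Does that person know the arm? |
|---|---|---|---|
| Manual cervical tests, thermal and pressure tests | Before randomisation | Examiner, with the patient's responses | No (Baseline measurements; Randomisation) |
| Baseline questionnaires | Before randomisation | Patient | No |
| HIT-6 (primary) | Follow-up | Patient | Yes |
| GPE (primary) | Follow-up | Patient | Yes |
| Frequency, intensity, medication, absenteeism, care-seeking (secondary) | Follow-up | Patient, in the Headache Inventory List | Yes |
| Entry of paper forms | Follow-up | Independent person | No, but this person rates nothing |

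The article does not say in so many words who scores the GPE. It is a perceived-effect scale, it stands among the online follow-up measurements, and no other assessor is named, so patient scoring is the only natural reading. No physical or observer-rated test is scheduled after randomisation. The arms differ visibly: under Interventions, UCMT adds up to 12 sessions of about 30 minutes, that is 12 × 30 = 360 minutes or 6 hours, with no matching contact in UC.

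**Step 2. The plan's own figure.** The inputs, from the statistical section, are 0.50 versus 0.70, significance level 0.05, power 80% and equal arms. With pooled variance under the null hypothesis, no continuity correction and a two-sided test:

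n = [1.960 × √(2 × 0.60 × 0.40) + 0.8416 × √(0.25 + 0.21)]² / 0.20² = [1.358 + 0.571]² / 0.04 ≈ 93 per arm, 186 in total.

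This reproduces the stated size. The article does not state sidedness. A one-sided test would give 74, so the two-sided reading is the one that fits.

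**Step 3. Illustration of consequence.** Assume no true effect (0.50 in both arms) and let knowledge of treatment raise the reported GPE responder rate in UCMT by b. The chance of a significant result favouring UCMT is

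Φ{ [b√93 − 1.960 × √(2p̄(1 − p̄))] / √(0.25 + p₂(1 − p₂)) }, with p₂ = 0.50 + b and p̄ = 0.50 + b/2.

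For b = 0.10: b√93 = 0.964, √(2 × 0.55 × 0.45) = 0.7036 and √(0.25 + 0.24) = 0.70. Then (0.964 − 1.379)/0.70 = −0.592, and Φ(−0.592) = 0.277.

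| Assumed shift b | Reported rates, UC vs UCMT | Chance of significance favouring UCMT |
|---|---|---|
| 0.05 | 0.50 vs 0.55 | 10% |
| 0.10 | 0.50 vs 0.60 | 28% |
| 0.15 | 0.50 vs 0.65 | 54% |
| 0.20 | 0.50 vs 0.70 | 80% |

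The comparator is 2.5%, the nominal error in that one direction of a two-sided 5% test. A shift of 0.20 equals the whole planned effect.

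**The case against.** The protocol is open about the treatment being unblinded, in the same sentence that claims blinded assessment, and it says that patients complete the questionnaires. A careful reader can work out the true position. That stands: the fault is a wrong label, not concealment. The authors also recognise patient preference as a source of bias. They exclude recent physiotherapy users and patients with recent changes in prescribed medication for that reason, and they return to preference in the Discussion. They do not connect it with self-rated outcomes, so the label remains uncorrected.

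Several stronger readings are tempting, and the document does not support them:

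- A reader might infer that the blinding arrangements protect against nothing. Self-completion removes interviewer influence, and blinded entry guards against transcription bias. What is missing is protection against response and expectation bias.
- A reader might extend the fault to the baseline questionnaires, where the article says "The rater is blinded: the online version is completed by the participants themselves". Those forms precede allocation, so nobody can know the arm and the statement is true there.
- A reader might infer that the primary aim is undermined to the same degree. That aim is the prognostic value of physical tests, whose predictors are measured blind before randomisation. That is a real safeguard, and the harm shown above concerns the comparison of arms, which is the secondary aim.
- A reader might count any response to the 6 extra hours of contact as bias. The question asked is the added value of physiotherapy on top of usual care, so contact effects are arguably part of the effect being estimated. They need to be stated, not removed.
- A reader might use headache frequency, medication and absence days as an independent check on GPE. The same unblinded patients report them.

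Whether the analyst works on coded arms may be settled in a document that is not shown, so its absence here is no fault.

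**Conclusion.** The point holds as a misstatement of the design. Study design and Follow-up measurements claim blinded assessment, while both primary and all secondary outcomes are reported by patients who know their arm. The blinding that exists covers baseline testing and data entry only.

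The size of any resulting bias cannot be derived from the document. The 10% to 80% range rests on assumed shifts of 5 to 20 points, a true response of 0.50 in both arms, full recruitment of 93 per arm and a two-sided 5% test. It shows how sensitive the GPE comparison would be and is not an estimate of what will happen. A reader might infer that a false positive is likely; nothing in the document supports a particular shift, so that does not follow.

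The correction should be made because it changes what the UCMT–UC comparison can claim. It does not make the trial unusable. Blinding patients is scarcely feasible in this comparison and is not asked for.

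**What to change.** Under Study design, replace the general claim of blinded assessment with one confined to baseline testing and data entry. Under Follow-up measurements, delete the statement that online availability ensures blinded rating, and describe GPE, HIT-6 and the Headache Inventory List as unblinded patient-reported outcomes. Self-completion and blinded entry of paper forms can still be credited with limiting interviewer and transcription bias.

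Add one sentence on interpretation: the UCMT–UC difference in GPE and HIT-6 is open to expectation and reporting bias, and it includes any effect of the extra contact.

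The cost is a few lines of text and a less favourable description of the design. Sample size, visits, instruments and patient burden are unchanged.

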#### Primary and secondary outcome measures

Two primary outcome measures will be used in this study: GPE and the HIT-6 score.

Reduction in headache frequency, headache pain intensity, medication intake, absenteeism and looking for professional help will be used as secondary outcome measures.

### Interventions

The UCMT group will receive a musculoskeletal physiotherapy treatment during 6 weeks following the protocol described by Jull et al. [10,11]. It consists of a combination of spinal mobilisations and exercise therapy. Spinal mobilisations consist of low and/or high-velocity cervical joint mobilization techniques. Each therapist can decide the technique of choice based on his own clinical skills and the patient's situation. Therapeutic exercises consist of low-load endurance exercises, more precisely cranio cervical flexion exercises. A maximum of 12 sessions (twice a week over a period of 6 weeks) is provided. Each session lasts approximately 30 minutes.

All participants receive a letter containing recommendations for treatment, based on the available evidence. This letter is to be handed over to the therapist. After the six weeks treatment period, the therapists will be contacted by phone to check for treatment integrity.

As a guideline for the UC treatment, the protocol from the Dutch College of GPs is used. It consists of a stepped approach to diagnose and treat primary headache disorders. In the Flemish part of Belgium this is the guideline with the lowest access threshold. The GP receives an email containing a weblink to the Dutch College of GPs guideline [7]. In this treatment group treatment integrity will be analysed via the Headache Inventory List, which is to be completed in the follow-up measurements.

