### Statistical analyses, power and sample size calculation

The prognostic capacity of the initial series of tests (physical examination of the cervical spine and QST) will be calculated by means of a logistic regression analysis, comparing the results of the responders with those of the non-responders. Instead of starting with a full regression model, two known prognostic factors, derived from the study from Jull and Stanton [8] will be included in the analysis a priori. Those two factors are 'light-headedness' and 'joint pain on palpation'. Consequently a backwards stepwise selection will be used, including the two known factors in the smaller models. Differences at baseline between the two treatment groups will be included in the regression models as potential prognostic factors. The plausibility of the signs will be considered to check the logical contribution of each factor in the model. The power of the obtained models will be analysed via the area under the ROC-curve.

Group differences and effect sizes can be calculated for headache intensity and frequency, medication intake, HIT-6 scores and absenteeism. The number of responders and non-responders in both groups will be compared. GPE is a dichotomous variable. Sample size calculations with a significance level of p < 0.05, an event rate of 0.50 in the usual care group and of 0.70 in the usual care plus musculoskeletal physiotherapy group a power of 80% and an equal amount of subjects in both treatment groups result in a sample size of 93 subjects in each treatment group. This results in a total of 186 subjects.

The results of all subjects will be analysed, regardless of their treatment adherence (intention-to-treat analysis).

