We preferred not to include generic questionnaires like the SF-36 in our outcome measures. This was mostly out of practical considerations: the initial set of questionnaires is quite long to complete. Adding another questionnaire can discourage patients to participate. The influence of migraine, tension-type headache and CEH on Quality Of Life (QOL) has been investigated before [41].

Quantitative Sensory Testing using thermal and pressure stimuli have been used to study patho-physiological mechanisms in headache patients [42-46]. General hypersensitivity has been demonstrated to be present in Whiplash patients with moderate to severe symptoms and not in recovered patients or those with mild symptoms [47]. This indicates the potential value of this test in predicting the evolution of a disorder.

The number of participants is the weak point of every clinical study. A pilot running from February 06 to June 06, with only first line recruitments resulted in 15 referred patients. To obtain the required number of patients the way of recruitment was adapted. Second line and advertisement recruitments were also included. The results will be analysed as in any multicenter trial: intercenter differences will be analysed to verify if patients can be pooled.

No training sessions dealing with the study protocol or treatments were organised for the participating medical doctors or therapists. This is a potential weakness of the study protocol. It was impossible to organize these sessions. The referring doctors receive no financial incentives or compensations whatsoever for participation in this study. They participate out of goodwill. Additional time investments would decrease this goodwill. We tried to have their commitment by informing them personally and by providing additional information on a website developed for that purpose [23].

The therapists could not be trained in advance either as it is not known in advance which therapists will participate. This depends on the patient's residence. Therefore the letter with treatment recommendations is provided.

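### The 93 per arm makes no allowance for therapist clustering, which arises in the physiotherapy arm only, so the stated 80% power rests on an unstated assumption of independent patients

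*Protocol article*

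**What the plan says.** In the Protocol article, Interventions, both arms receive usual care from the GP, and UCMT adds up to 12 sessions of mobilisation and exercise. On the mobilisation part, "Each therapist can decide the technique of choice based on his own clinical skills"; the sentence goes on to name the patient's situation as a second basis for the choice. Guidance to therapists is a letter that the patient hands over. After the six weeks, "the therapists will be contacted by phone to check for treatment integrity".

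The Discussion says therapists could not be trained because "it is not known in advance which therapists will participate", and that the therapist depends on where the patient lives. It plans a check of differences between centres before pooling, but mentions none between therapists.

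Statistical analyses, power and sample size calculation plans for responder rates of 0.50 under usual care and 0.70 under UCMT, tested at the 0.05 level with 80% power and arms of equal size. It arrives at "a sample size of 93 subjects in each treatment group", or 186 patients overall. Responder numbers are then to be compared between the groups. No design effect, number of therapists, patients per therapist or ICC appears.

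**The concern.** Patients treated by the same physiotherapist share that person's skill and, in part, preferred technique. If this moves outcomes, responses within a therapist are correlated and the UCMT responder rate has a larger variance than the binomial one. Nothing equivalent is added in the usual care arm, because GP care is common to both arms. The design is therefore partially nested, with clusters in one arm and individuals in the other.

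If the correlation is ignored, the power is below the stated figure and an unadjusted test rejects too often when physiotherapy has no average effect. Any interval built from that comparison would be too narrow. The comparison affected is the second research question, the additional value of physiotherapy. It is the secondary aim, but it is the only basis given for the sample size.

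**Working it through.** **Inputs from the article** (Statistical analyses, power and sample size calculation): responder rates 0.50 (usual care) and 0.70 (UCMT), significance level 0.05, power 80%, equal arms. Sidedness is not stated.

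**Inputs that must be assumed:** m, trial patients per therapist, and the therapist ICC. The article gives neither.

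**1. Reproduce the stated figure.** Two-sided, pooled variance under the null, no continuity correction, mean rate 0.60:

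n = [1.96 × √(2 × 0.60 × 0.40) + 0.8416 × √(0.25 + 0.21)]² / 0.20² = (1.358 + 0.571)² / 0.04 = 93 per arm.

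Power at 93 is 80.0%. The continuity-corrected version gives 103 and the one-sided version 74, so the article's number is the uncorrected two-sided one for independent patients. No reserve is left.

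**2. Add clustering in UCMT only.** With equal cluster sizes, the design effect is DE = 1 + (m − 1) × ICC. It multiplies the UCMT variance and leaves usual care unchanged:

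- SE under the null: √[0.24 × (1 + DE) / 93]
- SE under the alternative: √[(0.25 + 0.21 × DE) / 93]
- Power of a test that allows for the clustering: Φ[(0.20 − 1.96 × SE null) / SE alternative]
- True error of an unadjusted nominal 5% test: 2 × {1 − Φ[1.96 / √((1 + DE) / 2)]}
- Width of a correct interval relative to an unadjusted one: √[(0.25 + 0.21 × DE) / 0.46]

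**3. One case in full (m = 5, ICC 0.05).** DE = 1 + 4 × 0.05 = 1.20. SE null = √(0.528 / 93) = 0.0753. SE alternative = √(0.502 / 93) = 0.0735. Power = Φ[(0.20 − 0.1477) / 0.0735] = Φ(0.712) = 76.2%. Error = 2 × [1 − Φ(1.96 / 1.0488)] = 6.2%.

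**4. Range.** The last column only expresses size; it is not a request for more patients.

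| m | ICC | DE | Power at 93 | Error, unadjusted test | Relative interval width | n per arm for 80% |
|---|---|---|---|---|---|---|
| 1 | any | 1.00 | 80.0% | 5.0% | 1.00 | 93 |
| any | 0 | 1.00 | 80.0% | 5.0% | 1.00 | 93 |
| 2 | 0.05 | 1.05 | 79.0% | 5.3% | 1.01 | 96 |
| 3 | 0.05 | 1.10 | 78.1% | 5.6% | 1.02 | 98 |
| 5 | 0.01 | 1.04 | 79.2% | 5.2% | 1.01 | 95 |
| 5 | 0.05 | 1.20 | 76.2% | 6.2% | 1.05 | 103 |
| 5 | 0.10 | 1.40 | 72.5% | 7.4% | 1.09 | 112 |

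For scale, 93 UCMT patients at m = 2 means about 47 therapists (93 / 2 = 46.5), and at m = 5 about 19 (93 / 5 = 18.6).

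**The case against.** The best reply is that the clusters are likely to be small. Patients come from GP practices, two academic hospitals and advertisements. They take a letter to a therapist who depends on where they live, and no study clinic or panel of therapists is described. That points to many therapists with few trial patients each. At m = 2 and ICC 0.05 the loss is one point of power and 0.3 points of error. This stands, and it is why the effect is called probably modest. It does not settle the matter, because the article never says how many patients a therapist may take.

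Second, technique also follows the patient's situation, and the cited treatment protocol, the type of exercise, the session limit and the letter are common to all therapists. A reader might infer that all patients of one therapist get the same treatment. The text does not support that. It supports some shared influence of unknown strength, meaning an ICC that could be small.

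Third, the model for the arm comparison may sit in an analysis plan that is not shown, and the article names neither a test nor a confidence interval. This also stands. The absence of a therapist term is therefore not counted as an omission, and the remarks on error and interval width apply only if the comparison is made unadjusted. A later analysis plan cannot, however, put an allowance into a sample size already fixed without one.

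Finally, the number of responders per therapist may be too small to estimate a therapist variance. That limits which model is workable, and the fix allows for it.

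**Conclusion.** The point holds in a limited form. The 93 per arm is arithmetically right for independent patients and includes no allowance for therapist clustering in UCMT. The stated 80% power, and a 5% error rate for an unadjusted comparison, require about one trial patient per therapist or a negligible therapist ICC.

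For m from 2 to 5 with ICC 0.05, power is 79% to 76% and the unadjusted error 5.3% to 6.2%. At m = 5 with ICC 0.10 they are 73% and 7.4%. These figures assume equal cluster sizes and values of m and ICC that the article does not provide. Given assignment by residence, the lower end is more plausible.

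Two stronger readings should be resisted. A reader might infer that the power holds only if every therapist treats exactly one patient. That is not so: it holds at any cluster size when the ICC is zero, and the loss is under two points for m up to 3 with ICC up to 0.05. A reader might also infer that the trial is seriously underpowered. At m = 10 and ICC 0.10 power would be 64%, but nothing in the article suggests clusters of that size. Nor is the primary, prognostic aim shown to be affected.

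**What to change.** 1. Record the treating therapist for each UCMT patient. Therapists are already phoned for the integrity check, so this adds one identifier to the data set. Without it, clustering cannot be examined later.
2. Compare the arms with standard errors clustered on therapist, each usual care patient counting as a cluster of one. If clusters prove large enough to estimate a therapist variance, a partially nested model with a therapist random effect in UCMT only is an alternative.
3. In Statistical analyses, power and sample size calculation, say that the 80% assumes independent patients (one per therapist, or a negligible therapist ICC), and give the range above with its assumed values.

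No extra patients and no change to treatment are needed. The cost is an interval that may be slightly wider and a slightly less favourable statement of power. If most therapists treat a single patient, the clustered analysis costs almost nothing.

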**Methods/design:**

This trial is designed to identify patient characteristics which can influence the prognosis of the patient. Patients with recurrent headache and co-existent neck pain are recruited via a multicenter setup. After screening for eligibility, subjects are tested at baseline and randomly allocated to one of two treatment groups. Testing includes the administering of questionnaires (a Headache Diagnosis Questionnaire, Headache Inventory List and the Headache Impact Test (HIT-6)) and physical tests (Thermal Stimuli, Manual Cervical Spine Examination and Pressure Algometry). Treatment groups are a usual care group (UC) administered by the General Practitioner (GP) and a usual care plus musculoskeletal physiotherapy treatment group (UCMT). UC is based on the Dutch GP Guideline for Headache. UCMT consists of the UC plus a combination of exercises and spinal cervical mobilisations. Follow-up measurements consist of the completion of the Headache Inventory List, the HIT-6 and scoring of the global perceived effect (GPE). The latter allowing the distinction between responders (positive effect) and non-responders (no effect or worse). Logistic regression analysis will be used to identify the specific patient characteristics of the responders and the non-responders. The additional value of the musculoskeletal physiotherapy will be examined. Follow-up measurements up to 52 weeks are scheduled.

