### In- and exclusion criteria

Dutch speaking patients with a combination of recurrent headache and neck pain since minimum two months and at least twice a month with an active help-request (who consider to undergo treatment) are recruited. They have to be at least 18 years old and be willing to participate. Subjects are excluded in case of cluster headache or trigeminal neuralgia. To avoid false positive tests with the quantitative sensory tests (see description of measurements), patients with peripheral neuropathies and co-morbidity of chronic musculoskeletal pain will be excluded. Because of the neck mobility tests, people with rheumatoid arthritis, Down syndrome and/or a history of neck surgery will be excluded. The presence of red flags for headache (warning signs for serious causes of the headache) is an extra exclusion criterion. Pregnant women are also excluded, as pregnancy influences the frequency and intensity of headaches with migraine properties.

To avoid biased patients (with treatment preferences), we excluded patients who received physiotherapy treatment for their headaches during the last 12 months or patients whose prescribed medication was changed during the last two months.

The included headache types are migraine, tension-type headache and CEH. For migraine and tension-type headache the IHS criteria are used [26], for CEH the criteria of the Cervicogenic Headache International Study Group (CHISG) [27].

For the patients recruited via internet sites and advertisements, an additional exclusion criteria is set: a HIT-6 score of at least 56 points. From this level, the HIT-6 scoring advises the patient to contact his/her GP in order to start a treatment [28].

All subjects sign a written informed consent.

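### The described follow-up has no item on adverse reactions to treatment in either arm, and the responder comparison puts worsened and unchanged patients in one class

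*Protocol article*

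**What the plan says.** - **Treatment (Interventions).** "Spinal mobilisations consist of low and/or high-velocity cervical joint mobilization techniques". The choice is left to the therapist: "Each therapist can decide the technique of choice based on his own clinical skills", together with the patient's situation. At most 12 sessions are given, two a week for six weeks.
- **Preparation of therapists (Discussion).** "The therapists could not be trained in advance either as it is not known in advance which therapists will participate". The substitute is a letter: "Therefore the letter with treatment recommendations is provided".
- **Follow-up.** The Abstract gives a closed list: "Follow-up measurements consist of the completion of the Headache Inventory List, the HIT-6 and scoring of the global perceived effect (GPE". The Follow-up measurements section gives the times: "After approximately 7, 12, 26 and 52 weeks, participants will be asked to complete the Headache Inventory List and HIT-6 again". All questionnaires look back four weeks. The one longer look-back described is for absence days, over 12 months, at baseline and week 52.
- **Content of the Headache Inventory List.** It covers how often and how badly the head hurts, medication, care sought for headache, and absence days.
- **Outcomes (Primary and secondary outcome measures).** GPE and HIT-6 are primary. Five secondary outcomes follow, and none is a harm.
- **Responder definition (Follow-up measurements).** The seven-point GPE is cut so that patients who are unchanged and patients who are worse are both non-responders. The statistical section compares the arms on that split.
- **Therapist contact (Interventions).** "After the six weeks treatment period, the therapists will be contacted by phone to check for treatment integrity".

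**The concern.** The second research question is what physiotherapy adds to usual care. A full answer needs the reactions that the added treatment provokes as well as its effect on headache. As described, no instrument asks a patient in either arm whether treatment caused a reaction. A short-lived neck reaction, for example, has no field of its own. It could show only indirectly, through medication, care contacts or absence days, and only if it fell within the recall window.

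The data that can show deterioration of the headache itself are then coarsened in the main comparison. Two arms with the same responder rate could differ in how many patients became worse, and the planned comparison would not show it. At stake are a reaction rate by arm and a visible count of worsened patients, both of which bear on a referral recommendation.

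**Working it through.** **1. The plan's own sample size, to confirm that it is unaffected.** Inputs from the statistical section: 0.50 versus 0.70, alpha 0.05 (taken as two-sided), power 80%, equal arms. With pooled variance and no continuity correction:

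n = [1.960 × √(2 × 0.60 × 0.40) + 0.842 × √(0.50 × 0.50 + 0.70 × 0.30)]² / 0.20² = (1.358 + 0.571)² / 0.04 ≈ 93 per arm, 186 in total.

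This matches the stated figure. Recording reactions does not change it.

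**2. What each described source can capture.**
- *GPE, HIT-6, pain VAS:* deterioration of headache, without attribution to treatment.
- *Headache Inventory List:* more medication, more headache-related care, more absence days. No reaction item is described.
- *Therapist call:* treatment integrity. Its questions are not given. Sessions delivered and technique used could fit under that purpose; reactions and reasons for stopping early are not mentioned.
- *Outcome list:* no harm outcome.

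**3. What the responder split hides.** At the planned rates, non-responders number 93 × 0.50 = 46.5 under usual care and 93 × 0.30 = 27.9 with physiotherapy. The split alone is compatible with any number of worsened patients from none up to about 46 in the first arm and about 28 in the second.

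**4. Recall window.** Week 7 − 4 weeks = week 3. With two sessions a week and a start d weeks after the time origin, the sessions before the window number 2 × (3 − d):
- d = 0: 6 of 12
- d = 1: 4 of 12
- d = 2: 2 of 12

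The article calls the times approximate and does not state the origin or the start of treatment, so d is an assumption.

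**5. What recording could show.** The documents give no reaction rate, so a range is assumed. The chance of at least one affected patient among 93 is 1 − (1 − p)^93:
- p = 10%: 99.99%
- p = 5%: 99.2%
- p = 2%: 84.7%
- p = 1%: 60.7%
- p = 0.1%: 8.9%

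With no events in 93 patients, the one-sided 95% upper limit is 1 − 0.05^(1/93) = 3.2%. Exposure is at most 93 × 12 = 1,116 sessions, if every patient attends every session.

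**The case against.** The strongest reply is that this is a condensed article. Two ethics committees approved a research protocol that is not shown, and adverse-event recording is commonly left to such a document. That stands as a limit: the article cannot show that the full protocol lacks safety reporting, so the fix is conditional. It does not remove the point. The article gives its follow-up set as a closed list, itemises the main questionnaire, names every outcome and fixes the GPE split. Within what it fixes, reactions have no place and worsening is merged.

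Three stronger readings are tempting, and the article does not support them.
- *That physiotherapy is judged on benefit alone.* GPE, HIT-6 and VAS run in both directions, and medication, care and absence can rise. What is missing is recording of treatment reactions and a separate count of worsened patients.
- *That the therapists are unqualified.* The Discussion speaks of training in the study protocol and treatments, replaced by a letter. It says nothing against professional competence.
- *That the entry criteria conflict with the permitted techniques.* The article says "Because of the neck mobility tests, people with rheumatoid arthritis, Down syndrome and/or a history of neck surgery will be excluded". It gives no safety rationale, and these people are kept out of treatment as well as testing. Nothing here contradicts.

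On recall, the 12-month absence question at week 52 essentially spans the treatment course, but it counts only days off. A reaction that lasted into the window could still leave an indirect trace.

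**Conclusion.** The point holds in a limited form. The follow-up and outcomes as described have no item on adverse reactions in either arm, the responder comparison merges worse with no effect, and the week-7 recall may miss the first 2 to 6 of 12 sessions for start delays of two weeks down to none. Reactions at a true rate of 2% or more would probably be seen in 93 patients if asked about (84.7% chance or higher). Rare serious ones would mostly not be, so the gain is in common reactions.

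This rests on three assumptions: that the full protocol has no separate reaction record, that sessions run twice weekly, and that all 93 patients in the arm are followed. No stated figure is wrong, and the conclusion does not bear on which technique should be used. It is a cheap improvement worth making, not a fault that invalidates the design.

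**What to change.** Unless the full protocol already does so:
1. Add to the week-7 questionnaire, online and on paper, one item worded identically in both arms on adverse reactions to headache treatment since randomisation: what, when, how long, and whether treatment stopped because of it. Dating it from randomisation removes the dependence on the four-week window.
2. In the therapist call already planned, also record sessions given, technique used, any reaction, and the reason for stopping early. This source exists in the physiotherapy arm only, so it should describe that arm and not feed the comparison between arms.
3. Report patient-reported reactions by arm beside the responder comparison, and tabulate GPE worse separately from no effect by arm. The responder definition and the primary comparison stay as they are.

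Cost: one questionnaire item, four entries in an existing call and one table, with no extra visits and no change to 93 per arm. Downside: treatment is unblinded, so self-reported reactions may be given more readily for hands-on treatment, and the report should say so. No change to technique or clinical management is proposed.
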